**Background:**

As of December 2013, over 9 million people in Sub-Saharan Africa were receiving antiretroviral therapy (ART), representing a dramatic success for the ART roll-out that began in the early 2000s. However, this represents only 37% of all people living with HIV in Sub-Saharan Africa.^1^ There remains an urgent need to expand testing and treatment services to all patients requiring treatment and to retain those in care who are receiving ART. In Khayelitsha township outside of Cape Town, South Africa, an HIV treatment program was established in 2000 at three public sector primary care clinics serving 500,000 people. The program has since expanded to 11 clinics supplying ART to >30,000 patients. While the cumulative mortality of patients at one year of ART has decreased from 14.8% in 2001 to 1.7% in 2009, challenges remain in long -term provision of ART.^2^ As of 2009 in Khayelitsha, 87% of ART patients were alive and on ART at 12 months, 75.2% at 36 months, and 65% at 6 years, highlighting that strategies to retain patients in care could still improve.^2^ Analyses of the program from 2001-2007 indicated that 33% of persons lost to follow-up (LTFU) had in fact died. After correction for mortality, rates of LTFU at one year (in persons who had not died) increased from 0% in 2001 and 2003 to 1.7% in 2004, 3.8% in 2005, and 7.6% in 2007.^3,4^ Further data from 2010-2012 indicate that the probability of being LTFU increased during this period compared to previous calendar periods.^5^ In order to address this issue of LTFU in Khayelitsha, it is necessary to identify modifiable risk factors for default from ART and the outcomes of these patients so that interventions can be appropriately targeted to improve long–term retention and reduce mortality in this patient population.

The current UCT HRC approved protocol “*Enhanced routine surveillance of patients in HIV care in Khayelitsha*” outlines the unique contribution of the Khayelitsha cohort data in light of Khayelitsha’s status as one of the longest standing and largest HIV treatment programmes in South Africa. The proposed sub-study falls under the purview of continued collaborative analyses to assist in service delivery in Khayelitsha and other areas around South Africa. Linkage of the Khayelitsha cohort to mortality data (as approved by HREC 137/2008) will also contribute to this aim.

**Aims and Objectives / Purpose of the Study**

In a meta-analysis of 15 ART programs in sub-Saharan Africa, Brinkhof et al. (2009) found that the percentage of patients lost to the programs ranged from 5 to 50% and mortality ranged from 12-87% of patients LTFU. In addition to deaths, the most common reasons for patients not returning to clinic were financial problems, deteriorating or improving health, and transfer to another program. In a qualitative study from South Africa, Miller et al (2010) found that transport and logistical barriers in clinics (including patient-friendly clinic hours) contributed to default from ART care. In line with this previous research, our hypothesis for this study is that logistical barriers in clinics, as well as individual demographic and health factors contribute to loss to follow up from ART care and subsequent morbidity and mortality, as measured by hospitalizations and vital status.

The specific aims of this study will be to 1) identify the clinics at which the highest incidence of default is occurring in Khayelitsha, 2) identify risk factors for default from ART care, and 3) determine the outcomes of patients who default on ART. In doing so, this study will aim to identify both patient and clinic factors for which future interventions could be directed to reduce default (see below for a list of potential risk factors).

**Methodology**

*Study Design:*

Default from ART care will be defined as failing to attend a follow-up appointment at an ART clinic > three months after the last appointment. We will perform two inter-related studies:

1) Retrospective cohort study**:** The cohort will be all patients attending ART clinics in Khayelitsha at least once between 1 January 2014 – 31 December 2014. This cohort will include persons who have been on ART for varying lengths of time. We will determine the incidence of default from ART care during this time period in Khayelitsha as a whole and by ART clinic, allowing a 3- month buffer into 2015 to those patients presenting to clinics late in the calendar year to allow for the possibility of default during this time. We will describe the demographic and clinical characteristics of the patients who default and the distribution of durations on ART when default occurs. Utilizing clinic records and databases, the national death register, and the ongoing Khayelitsha cohort study directed by one of my mentors [name], we will also determine outcomes of the patients who defaulted in terms of return to another ART clinic in Khayelitsha, admission to the Khayelitsha Hospital (and admission diagnosis), death, and the timing of these outcomes in relation to ART default. The use of a unique identifier across the different electronic data platforms that are used to capture clinical data from the hospital and HIV and TB clinics in Khayelitsha will allow us to link databases and establish these outcomes.

2) Nested case-control study: To determine risk factors for LTFU, we will randomly select 200 patients who defaulted ART, and select one control patient (who did not default ART) for each case, matched for ART clinic and calendar year in which the patient started ART. We will extract from the clinic records for these cases and controls demographic and clinic variables (e.g., age, gender, area of residence, marital status, employment status, baseline CD4, ART prescribed, first versus second line ART, ART side effects, TB treatment, psychological complaints, substance abuse, physical symptoms, collecting medication monthly or every 3 months, belonging to a treatment support club or not). Other variables such as economic factors are not currently in the databases and will not be able to be included in the analysis.

*Sample size assumptions and estimates:*  Nested case-control study: In order to detect an odds ratio of 2.5 for variables that have a prevalence of 10% among controls (e.g. second line ART or alcohol abuse, both of which have prevalence of ~10% in this cohort based on previous studies), a sample size of 388 (194 pairs) is required (alpha = 0.05; power = 0.90). We therefore plan to include 200 pairs in this study. There are over 30,000 adult patients on ART in Khayelitsha. Given the percentage of patients defaulting ART described above, we anticipate sufficient numbers for this study.

*Characteristics of the study population:* The study population will comprise all patients on ART in the Khayelitsha clinic system of over 30,000 patients. The research will be retrospective, based at the University of Cape Town, with some travel to the Khayelitsha clinics to obtain missing data.

*Recruitment and enrollment of participants:* We will utilize patient records from electronic and paper data management systems that cover the clinics in Khayelitsha.

*Research procedures and data collection methods:* Data will be extracted from existing electronic and paper medical and hospital records, and the national death registry. Patients will not be contacted nor will informed consent be obtained due to the anonymity of the study.

*Intervention:* This study aims to identify risk factors at which future interventions can be directed in the Khayelitsha clinics to reduce default from ART care. This specific study will not seek to carry out any interventions, but the manuscripts emanating from the study will propose future interventions. [name] holds a position in the provincial government and this will assist in reporting findings back to policy makers.

*Data analysis plan:* The data will be analyzed using STATA and GraphPad Prism software programs. For the case-control study, for each exposure variable we will calculate the odds ratio for default in univariate analysis. Variables associated with the outcome with p-value <0.1 and certain *a priori* variables will be entered into multivariate logistic regression models to determine independent risk factors for ART default.

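### A fixed three-month gap defines default for everyone, so the outcome depends on the medication collection interval, which is itself a studied exposure

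*Protocol*

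**What the plan says.** The Study Design text under Methodology in the Protocol defines default as "failing to attend a follow-up appointment at an ART clinic > three months after the last appointment". It does not say whether the appointment that starts the clock is the last one attended or the last one scheduled, and the threshold does not vary with the planned visit interval.

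The cohort covers patients seen in calendar 2014, with a "buffer into 2015 to those patients presenting to clinics late in the calendar year to allow for the possibility of default during this time".

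The nested case-control study lists among its exposures "collecting medication monthly or every 3 months, belonging to a treatment support club or not". The plan is to "select one control patient (who did not default ART) for each case", "matched for ART clinic and calendar year in which the patient started ART". Collection interval is not a matching factor.

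Under the Data analysis plan, each exposure gets a univariate odds ratio. Those with p below 0.1, plus some a priori variables, go into multivariate logistic regression. No sensitivity definition of default is given.

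**The concern.** Patients with different planned gaps between visits are judged against the same elapsed time. If that time runs from the last attended visit, a monthly collector must miss the due visit and about two more before counting as a defaulter. A 3-monthly collector can qualify by being a few days late once. Nothing in the Protocol says that a later return cancels the default; return to another ART clinic is instead listed as an outcome after default.

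The label then means different things in the two groups of a comparison that the study sets out to make. Collection interval is a feature of the service that could be changed, and the Protocol intends to report its findings to policy makers, so an association created by the definition could mislead. Cases and controls are also selected by this definition, so an error in it is hard to undo once charts have been extracted.

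**Working it through.** **The plan's own figure.** The sample size text (OR 2.5, 10% exposed among controls, alpha 0.05 taken as two-sided, power 0.90) gives 194 pairs.
- Exposure among cases: 2.5 × 0.10 / (1 + 0.10 × 1.5) = 0.2174.
- P = 2.5/3.5 = 0.714. Discordant pairs: [1.96/2 + 1.2816 × √(0.714 × 0.286)]² / (0.714 − 0.5)² = 52.9.
- Probability of discordance: 0.10 × 0.7826 + 0.2174 × 0.90 = 0.274. Pairs: 52.9/0.274 = 193.2, rounded up to 194.

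The figure reproduces and this point does not affect it. The OR of 2.5 serves below only as a yardstick.

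**Grace under a clock from the last attended visit.** Grace = threshold − planned interval. The threshold of three months is about 91.3 days. The interval lengths in days are assumptions.

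| Collection | Interval (days) | Grace (days) |
|---|---|---|
| Monthly | 28 | 63.3 |
| Monthly | 30.4 | 60.9 |
| 3-monthly | 84 | 7.3 |
| 3-monthly | 90 | 1.3 |
| 3-monthly | 91.3 | 0 |

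This contrast needs no assumption about how patients behave.

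**Which reading the buffer fits.** Take a patient last seen on 31 December 2014.
- Clock from the attended visit: three months end on 31 March 2015, exactly the buffer, for both collection intervals.
- Clock from the next scheduled, missed visit: a monthly collector is due in late January and classifiable in late April 2015. A 3-monthly collector is due in late March and classifiable in late June 2015. Both dates lie beyond the buffer, by about one and three months.

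**Effect on the odds ratio (illustration; the lateness inputs are not in the Protocol).** Assume the same true default d in both groups, a share L of visits late, exponential delay with mean m days, independent visits, and 12 or 4 visits a year (k).
- False label per visit: q = L × exp(−grace/m).
- Labelled within a year: 1 − (1 − d)(1 − q)^k.

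Worked case, d = 8%, L = 5%, m = 7:
- Monthly (30.4 days): q = 0.05 × exp(−60.9/7) = 0.0000083; labelled 0.080.
- 84-day: q = 0.05 × exp(−7.3/7) = 0.0176; labelled 1 − 0.92 × 0.9824⁴ = 0.143; OR against monthly 1.9.
- 90-day: q = 0.05 × exp(−1.3/7) = 0.0415; labelled 1 − 0.92 × 0.9585⁴ = 0.224; OR 3.3.

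Over d = 5% to 15%, L = 5% to 20%, m = 7 or 14 and 84- or 90-day supply, the extremes are:
- lowest: d = 15%, L = 5%, m = 7, 84-day: 0.208 against 0.150, OR 1.5;
- highest: d = 5%, L = 20%, m = 7, 90-day: 0.541 against 0.050, OR 22.

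The true OR is 1 throughout.

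**The case against.** The strongest reply is that the Protocol never says the clock starts at an attended visit. If it starts at the last scheduled, missed one, grace is equal and the unequal tolerance disappears. Default could also be dated at the missed appointment: one missed by 31 December 2014 is classifiable by 31 March 2015, and the buffer is then long enough. This stands to the extent that the wording is open. But the buffer is offered to patients who present late in 2014 so that they can still default. Someone seen at the end of December, and next due in 2015, could not do so under that dating. The attended-visit reading fits best but is not certain. If the scheduled reading holds and late presenters are to be classified, the bias reverses, because 3-monthly collectors are the harder to classify.

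The size is also fairly challenged. Late-visit frequency, delay distribution and supply length are all assumed, so the range above is an illustration and not an estimate for this cohort.

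A reader might also infer wider damage than the Protocol supports:
- That odds ratios for club membership, clinical stability or time on ART are distorted. No link between clubs and collection interval is stated, stability and duration are not among the listed exposures, and controls are matched on year of ART start. Distortion that reaches other exposures through collection interval can largely be adjusted for if interval enters the model.
- That clinics with more 3-monthly supply will rank worse. This needs clinics to differ in that share, and the Protocol gives no such data.

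What the reply does not remove is the effect on collection interval itself. Matching does not involve it, and regression cannot correct an outcome misclassified according to that very exposure.

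**Conclusion.** The point holds as a defect in how default is defined. On the best-fitting reading, grace after the due date is about 61 to 63 days for monthly and 0 to 7 days for 3-monthly collectors. The outcome is then differentially misclassified by a studied exposure, and the odds ratio for 3-monthly collection is biased upward. The direction follows from the definition. The amount does not, because it rests on lateness that the Protocol does not report; in a mild assumed case it is about 1.9 to 3.3, comparable with the 2.5 the study is powered to detect. Clinic incidence in Aim 1 is distorted only if clinics differ in their share of 3-monthly collectors.

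On the other reading, grace is equal but the buffer is too short for patients last seen late in December 2014, and by a different amount for each interval. On both, whether a patient is counted as a defaulter depends on collection interval. The Protocol does not support a claim that the study would necessarily find 3-monthly collection harmful, or any single figure for the share of patients mislabelled.

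**What to change.** Before cases and controls are selected:
1. Define default as no attendance at any ART clinic for one fixed period, for example 3 months, after the date the patient was next due (scheduled visit or end of dispensed supply), the same for every collection interval. State how default is dated.
2. Extend the follow-up cut-off to 30 June 2015 for the whole cohort. Extending it only for 3-monthly collectors would leave monthly collectors seen at the end of December unclassifiable, since they need follow-up to about late April.
3. Keep the fixed gap from the last visit as a sensitivity analysis, and report the collection-interval odds ratio under both definitions.

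The cost is a later extraction date from the same retrospective sources, plus deriving due dates. The second is the larger task. Default has to be classified across the whole cohort, drawn from a population of over 30,000, whereas the Protocol describes extracting collection interval only for the 200 pairs. Where no due date is recorded it must be imputed from the supply dispensed, and the rule for doing so should be written down.

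### Patient-level risk factors for default are compared only in 200 matched pairs; for exposures held electronically, a cohort-wide comparison with non-defaulters would add much precision at little cost.

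*Protocol*

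**What the plan says.** The second specific aim is to find risk factors for default. Methodology, Study Design, gives that task to the nested case-control study: "To determine risk factors for LTFU, we will randomly select 200 patients who defaulted ART, and select one control patient", matched on ART clinic and on the year ART was started. The only regression in the data analysis plan is for that study.

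The cohort arm covers every patient who attended a Khayelitsha ART clinic in 2014. It gives the incidence of default overall and by clinic. For patient characteristics it says only: "We will describe the demographic and clinical characteristics of the patients who default". No comparison with retained patients is planned.

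On data sources, the case-control variables are to be extracted from clinic records, sources are both electronic and paper, and clinic visits are foreseen for missing items. Economic factors are left out for this reason: "Other variables such as economic factors are not currently in the databases and will not be able to be included in the analysis". On scale: "There are over 30,000 adult patients on ART in Khayelitsha".

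The sample size paragraph aims to "detect an odds ratio of 2.5 for variables that have a prevalence of 10% among controls" ("alpha = 0.05; power = 0.90"), finds that "a sample size of 388 (194 pairs) is required", and concludes: "We therefore plan to include 200 pairs in this study".

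**The concern.** Default status has to be established for every 2014 attender, because incidence is reported for the whole cohort. The plan to describe all defaulters, and the reason given for omitting economic factors, both imply that at least some of the listed characteristics are in the linked databases. For those variables the protocol gives no reason to limit the comparison of defaulters with non-defaulters to 400 people. A sample is well justified for items that must be read from folders, which may include substance abuse, psychological complaints and side effects.

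A table of defaulters alone gives the mix among defaulters. Without the mix among non-defaulters, or the default rate per category, it cannot show higher or lower risk.

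The results are meant to direct interventions and to be reported to policy makers. A null finding from a sample with low power could be read as evidence that a factor does not matter.

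**Working it through.** **Inputs from the protocol.** Odds ratio (OR) 2.5; exposure among controls p0 = 0.10; alpha 0.05 (two-sided assumed, as the protocol does not say); power 0.90; 200 pairs; over 30,000 patients on ART. The 2014 default rate is not given. The Background reports one-year loss to follow-up, corrected for mortality, of 1.7% (2004), 3.8% (2005) and 7.6% (2007), and says that the probability rose later.

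**Assumptions.** Cohort N = 30,000. Default 1.7% to 15%, where 15% is an illustrative upper value. Case and control exposure independent within pairs. Cohort figures are unadjusted, with complete data.

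**Step 1: the plan's own figure.** Exposure in cases: p1 = OR·p0/(1 − p0 + OR·p0) = 0.25/1.15 = 0.2174. Probability that a pair is discordant: pd = p1(1 − p0) + p0(1 − p1) = 0.1957 + 0.0783 = 0.2739. With P = OR/(1 + OR) = 0.714, discordant pairs needed = (0.98 + 1.282·√[P(1 − P)])²/(P − 0.5)² = 52.9. Pairs = 52.9/0.2739 = 193.2, rounded up to 194. The stated figure reproduces.

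**Step 2: power with 200 pairs.** Power = Φ{[√(200·pd)·(P − 0.5) − 0.98]/√[P(1 − P)]}.

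| Exposure in controls | OR 1.5 | OR 2.0 | OR 2.5 |
|---|---|---|---|
| 10% | 25% | 65% | 91% |
| 30% | 48% | 92% | >99% |
| 50% | 52% | 93% | >99% |

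For example, at 10% exposure and OR 1.5, pd = 0.2143, so 42.9 discordant pairs are expected and power is 0.253.

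**Step 3: the full cohort at 10% exposure.** With D defaulters and C = 30,000 − D others, SE(ln OR) = √[1/(D·p1) + 1/(D(1 − p1)) + 1/(C·p0) + 1/(C(1 − p0))]. The OR detectable with 90% power solves ln OR = (1.960 + 1.282)·SE. At OR 1.5 the same SE formula with 200 cases and 200 controls gives 0.310.

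| Default | Defaulters | Detectable OR, 90% power | SE at OR 1.5 | 0.310 ÷ SE |
|---|---|---|---|---|
| 1.7% | 510 | 1.51 | 0.128 | 2.4 |
| 7.6% | 2,280 | 1.24 | 0.063 | 4.9 |
| 15% | 4,500 | 1.18 | 0.047 | 6.5 |

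For example, at 7.6% the four expected cells at OR 1.5 are 325.7, 1,954.3, 2,772 and 24,948, and the SE is √0.00398 = 0.063. A two-proportion sample-size formula gives slightly larger detectable values: 1.55 at 1.7% default and 1.25 at 7.6%.

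**Step 4: would more controls do instead?** With 200 cases and four controls each, the OR detectable with 90% power at 10% exposure falls only from 2.51 to 2.08 (two-proportion formula). The number of cases is the limit, and the cohort has more of them.

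**The case against.** A nested case-control sample is a standard design when records must be abstracted, and this one meets its declared target. That stands: the sample size arithmetic is right, and nothing here is a contradiction in the protocol.

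The protocol also does not say which covariates are electronic for non-defaulters, or how complete they are. Linkage is described as a means of establishing outcomes, not of assembling covariates. That stands too. A reader might infer that the databases already hold all the listed variables for the whole cohort. The text supports only that they hold some of them, so any cohort-wide model must be conditional.

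Joint adjustment would suffer. The matched sample holds all variables together, whereas a cohort model could not adjust for record-only items. Regimen and TB treatment can change over time, so the timing of exposure must be fixed. Both points stand and shape the fix.

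Further cohort analyses could be left to a statistical analysis plan, which is not at hand. This carries less weight: the protocol itself assigns the risk-factor aim to the pairs and limits the characteristics table to defaulters.

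**Conclusion.** The point holds as a cheap improvement, not as an error. Patient-level risk factors are compared only in 200 pairs, and associations near OR 1.5, or near OR 2.0 for exposures of about 10%, will often go undetected. For electronically held exposures, a cohort comparison would cut standard errors by a factor of about 2.4 to 6.5. This rests on 30,000 patients, 10% exposure, default between 1.7% and 15%, and complete unadjusted data; missing values and adjustment would reduce the gain.

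Two stronger readings are tempting, and the documents do not support them:

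- **That moderate risk factors will be missed outright.** OR 2.0 has 65% power at 10% exposure and over 90% at 30–50%, and OR 1.5 is close to a coin toss for common exposures.
- **That the cohort arm looks at defaulters alone.** It reports incidence for everyone and by clinic; only the characteristics table is limited to defaulters.

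**What to change.** First list which exposures are held electronically for both defaulters and non-defaulters. For those:

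1. Tabulate defaulters beside non-defaulters, with the default rate per category.
2. Add a cohort-wide regression of default that includes clinic and either ART start year or time on ART, with exposures measured before default. This also lets ART start year be studied, which the pairs cannot do because they are matched on it.

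Keep the 200 matched pairs for variables that need record abstraction and for the jointly adjusted model.

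The cost is analysis time on data already being linked; for these exposures no further abstraction is needed. There are three downsides. Routine fields will have some missing values. The cohort model cannot adjust for record-only variables such as substance abuse or side effects. The two sets of estimates differ in adjustment and must be clearly labelled.

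### The case-control study is matched and sized in pairs, but the stated analysis does not carry the matching through, which can pull odds ratios toward 1 for exposures linked to clinic or ART start year

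*Protocol*

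**What the plan says.** All of this is in the protocol, under Methodology.

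- **Study Design, nested case-control study.** For 200 randomly selected defaulters, the investigators will "select one control patient (who did not default ART) for each case", "matched for ART clinic and calendar year in which the patient started ART".
- **Sample size assumptions and estimates.** The aim is to "detect an odds ratio of 2.5 for variables that have a prevalence of 10% among controls", with second-line ART and alcohol abuse as the two examples. The result is that "a sample size of 388 (194 pairs) is required (alpha = 0.05; power = 0.90"), followed by "We therefore plan to include 200 pairs in this study".
- **Data analysis plan.** First, "for each exposure variable we will calculate the odds ratio for default in univariate analysis". Then variables with p<0.1, plus certain a priori variables that are not named, are "entered into multivariate logistic regression models to determine independent risk factors for ART default".

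The data analysis plan does not mention pairs, a matched-pair odds ratio, McNemar's test, a conditional model, or clinic and start year as covariates. It does not use the word unconditional either.

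**The concern.** Matching in a case-control study changes the make-up of the control group. Controls are chosen to resemble cases on clinic and start year, so they also come to resemble them on any exposure that varies with clinic or start year. An analysis that pools cases and controls without regard to the matching then understates the association for those exposures.

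The entry rule does not repair this. With exact 1:1 matching, clinic and start year have the same distribution in cases and controls. Their crude association with default is nil by construction, so they cannot qualify at p<0.1. They would enter only if they were on the unnamed a priori list.

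The study's second aim, identifying risk factors for default, rests on this analysis, and the findings are meant to reach policy makers. A real risk factor could be reported as weaker than it is, or dropped at the univariate screen.

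**Working it through.** **Inputs from the protocol.** Odds ratio ψ = 2.5; exposure among controls p0 = 0.10; alpha 0.05 (sidedness not stated; 194 reproduces as two-sided); power 0.90; one control per case; 200 pairs planned.

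**Step 1: reproduce 194 pairs.** Matched-pair (McNemar) formula with independent exposures within a pair:

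- Exposure in cases: p1 = 2.5 × 0.1 / (1 + 0.1 × 1.5) = 0.25 / 1.15 = 0.2174.
- Probability that a discordant pair has the case exposed: P = 2.5 / 3.5 = 0.714.
- Discordant pairs needed: m = [1.96/2 + 1.2816 × √(P(1−P))]² / (P − 0.5)² = 52.93.
- Probability that a pair is discordant: p1(1−p0) + p0(1−p1) = 0.1957 + 0.0783 = 0.2739.
- Pairs: 52.93 / 0.2739 = 193.2, so 194. This matches the protocol.

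A standard two-sided unmatched comparison (pooled variance) needs 202 per group, or 219 with continuity correction. An unpooled version needs 199. The stated figure therefore comes from a matched calculation with within-pair exposure correlation φ = 0.

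**Step 2: allow φ above 0.** The protocol gives no φ, so the values below are assumptions. The conditional odds ratio stays at 2.5 and p0 at 0.10. With k = φ√(p0(1−p0)p1(1−p1)), the discordant probabilities are b = p1(1−p0) − k and c = p0(1−p1) − k, and p1 is solved so that b/c = 2.5. Then:

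- odds ratio targeted when pairs are ignored = p1(1−p0) / [p0(1−p1)];
- matched power = Φ{[√(200(b+c)) × (P − 0.5) − 1.96/2] / √(P(1−P))};
- pair-ignoring power = Φ{[(p1−p0) − 1.96 × SE0] / SE1}, where SE0 = √(2p̄(1−p̄)/200), p̄ is the mean of p1 and p0, and SE1 is the standard error of p1−p0 under the alternative. The lower power figure takes SE1 as if the groups were independent. The higher uses the paired variance [(b+c) − (p1−p0)²]/200.

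Example at φ = 0.1: p1 = 0.2017, b = 0.1695, c = 0.0678, b + c = 0.2373. The pair-ignoring odds ratio is 0.2017 × 0.9 / (0.1 × 0.7983) = 2.27.

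| Assumed φ | OR ignoring pairs | Power ignoring pairs, 200 pairs | Matched power, 200 pairs | Pairs for 90% matched power |
|---|---|---|---|---|
| 0 | 2.50 | 89.8% | 91.0% | 194 |
| 0.05 | 2.38 | 86.0–86.6% | 88.9% | 208 |
| 0.1 | 2.27 | 81.3–82.6% | 86.4% | 224 |
| 0.2 | 2.07 | 69.9–72.0% | 80.3% | 262 |

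**Step 3: simulation check.** In 4,000 simulated studies of 200 pairs with true odds ratio 2.5, the median pair-ignoring odds ratio was 2.27 at φ about 0.11 and 2.07 at φ about 0.21. Pair-ignoring power was about 83% and 71%, and McNemar power about 86% and 79%. With a true odds ratio of 1, the pair-ignoring test rejected 3.7% of the time at φ about 0.09 and 3.0% at about 0.19, against a nominal 5%. The test is conservative.

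**The case against.** **The text does not say unconditional.** Conditional logistic regression is a form of logistic regression, Stata fits it, and the unnamed a priori variables might include clinic and start year. A reader might infer that the protocol has chosen an ordinary unmatched model; the document does not say so. What stands against this defence is that the protocol states its univariate measure, its model and its entry rule, and none of them takes up the matching. An analyst following the text would have no instruction to use the pairs.

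**The bias is not general.** A reader might infer that every odds ratio will be attenuated. At φ = 0, the protocol's own sizing assumption, the pooled odds ratio is exactly 2.50. Attenuation needs an exposure related to clinic or start year. That is plausible for second-line ART or support-club membership; the protocol gives no ground for assuming it for gender or alcohol abuse, for instance.

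**The power claim does not collapse.** A reader might infer that the stated analysis cannot deliver 90%. On the protocol's inputs, ignoring the pairs gives 89.8% with 200 pairs. Where φ exceeds 0, the correct matched analysis also falls short, so part of the loss comes from sizing at φ = 0. The part due to ignoring the pairs is the gap between the two power columns: about 2 to 3 points at φ = 0.05, 4 to 5 at 0.1 and 8 to 10 at 0.2.

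**Large φ needs strong clustering.** Suppose exposure prevalence varies across clinic-by-year strata as a beta distribution with mean 10%. An intraclass correlation of 0.2 (φ about 0.23, pair-ignoring odds ratio 2.01) needs a standard deviation of √(0.1 × 0.9 × 0.2) = 13.4 percentage points. An intraclass correlation of 0.05 (φ about 0.07, odds ratio 2.35) already has a 10th-to-90th percentile range of 3% to 19%. The upper rows of the table are therefore demanding scenarios. This objection stands as a limit on size, not on the mismatch itself.

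**The error is conservative.** It creates no excess of false risk factors. That is true, but it lowers the chance of finding real ones.

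**Conclusion.** The point holds in conditional form. The design is individually matched and the sample size comes from a matched-pair formula, but the written analysis does not carry the matching through, and its p<0.1 screen cannot bring the matching factors in. This is a stated analysis that does not fit the stated design, rather than a detail left to a later plan.

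If the text is followed as it stands, odds ratios for exposures correlated with clinic or start year are pulled toward 1 and their tests are conservative. For a true odds ratio of 2.5 and 10% control exposure, the shift is to about 2.38 at φ = 0.05 and 2.07 at φ = 0.2, with nothing lost at φ = 0. These sizes rest on assumed φ, because the protocol reports none. The documents do not support a claim that all estimates for the second aim are biased, or that the 90% power fails on the protocol's own inputs.

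**What to change.** Two sentences in the Methodology section:

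1. In the data analysis plan, state that univariate and multivariable odds ratios come from conditional logistic regression grouped on the matched pair or on the clinic-by-start-year stratum. Alternatively, specify unconditional logistic regression with clinic and ART start year forced into every model, including the univariate screen.
2. In the sample size paragraph, state that 90% power assumes zero within-pair exposure correlation, and give matched power for 200 pairs as about 91%, 86% and 80% at correlations of 0, 0.1 and 0.2.

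The data, software and number of pairs do not change. The cost is a slightly less favourable power statement for exposures that cluster by clinic or start year.
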